**Methods/design:**

This is a randomized, prospective, double-blind, placebo-controlled, multicenter trial, which is stratified by puberty and sex. Eighty pre-pubertal (40 boys and 40 girls) and 80 pubertal non-diabetic obese children (40 boys and 40 girls) are being recruited in four Spanish Clinical Hospitals. The inclusion criteria to participate in the RCT include a Body Mass Index (BMI) above the 95th percentile and age 7–14 years. The pubertal stage is determined based on the Tanner criteria. Participants are assigned to two groups in accordance with a randomization schedule and receive 1 g of metformin or placebo for six months in combination with healthy lifestyle recommendations in both groups. The primary outcomes include changes in the BMI Z score and the biomarkers associated with the early appearance of insulin resistance syndrome, inflammation, cardiovascular risk according of the presence of genetic determinants of metformin response, as well as possible modifications in microbiota.

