## Methods

### Objectives

In accordance with the previously discussed background, the present study has four main objectives: the first objective is to determine the efficacy of metformin in combination with a lifestyle intervention in reducing BMI in obese children compared with placebo after 6 months; the second objective is to evaluate the effects on insulin resistance inherent to metabolic syndrome; the third objective is to identify its effects on inflammatory, cardiovascular risk and oxidative stress biomarkers; the fourth objective is to evaluate the change of gut microbiota composition after treatment. Additionally, metformin differential response will be analyzed according to genetic polymorphisms in drug uptake transporter genes.

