### Blood, urine and fecal sampling

General biochemical analyses are performed at the participating hospitals following internationally accepted protocols.

Blood samples are obtained for biochemical and hematological screening tests between 08.30 and 10.30. Three milliliters of blood are collected at the beginning and at the end of the trial. The blood is drawn via the antecubital vein. Peripheral white blood cells (buffy coat) are taken for deoxyribonucleic acid (DNA) extraction. Moreover, a 1-ml urine sample is obtained for oxidation marker analysis. Children should not eat for 12 hours before the sampling. All samples are collected and stored frozen by the research staff. The samples will be analyzed in the clinical laboratory of each hospital, as well as the INYTA.

In order to studying the childrens’ gut microbiota, 100–200 g of fecal sample is collected in a sterile container by parents at the beginning and at the end of the trial. Immediately, all samples are stored frozen until to be analyzed at the INYTA.

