### Statistical analysis

Data will be analyzed using SPSS software version 22 for Windows. Descriptive statistics for all outcomes will be determined. A Kolmogorov-Smirnov test will be used to test data normality. Data that are not normally distributed will be transformed by means of a log10 or square root for analysis. The homogeneity of variances will be determined with a Levene’s test. Normally distributed data will be reported as mean ± standard deviation (SD) and nonparametric data as median (range). The analysis selected to determine the effect of treatment is a linear mixed effects model (LMM), for which the center is considered covariance to adjust the statistical analysis. The fixed effects include time, treatment, adherence, puberty, sex, the interactions *time × treatment*, *time × treatment × puberty* and *time × treatment × sex*. A Bonferroni test will be used to assess the specific differences between the treatments.

Regarding genetic variations, linear regression will be performed to analyze differences in principal variable changes between genotypes and to evaluate independent associated factors.

Moreover, the raw microbiologic data are reported as relative abundances. Differences among times, treatments and puberty are compared using the Mann-Whitney *U* test. Finally, the clustering of the colonic microbiota in both of groups is calculated by a principal component analysis.

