#### Microbiota analysis

The fecal samples are subjected to extracting and purifying microbial DNA by a specific commercial DNA kit for purification (QIAamp DNA Stool Mini Kit, Quiagen, Barcelona, Spain). Quantification is conducted with a NanoDrop ND-1000 spectrophotometer (Thermo Fisher Scientific, Newark, DE, USA) in the Department of Microbiology, University Hospital San Cecilio (Granada, Spain). Polymerase chain reaction (PCR) is performed in a FastStart High Fidelity PCR System, dNTP Pack (Roche Applied Science). After PCR, amplicons are further purified using AMPure XP beads (Beckman-Coulter) to remove smaller fragments. DNA concentration and quality are measured using a Quant-iT™ PicoGreen® dsDNA Assay Kit. Afterwards, pyrosequencing of the PCR amplicons is performed using a Roche/454 GS Titanium technology platform (Roche, Branford, CT, USA). The MG-RAST (metagenomics analysis server) and the Ribosomal Database Project are used for the taxonomic analysis. Metagenomics data will be deposited in the publicly available repository MG-RAST (http://metagenomics.anl.gov/).

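### The microbiota objective is given single-abundance Mann-Whitney tests and a PCA that tests nothing, with no stated between-arm comparison of change and no stated error control across taxa

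*Protocol article*

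**What the plan says.** The Objectives section states that "the fourth objective is to evaluate the change of gut microbiota composition after treatment". The abstract's sentence on primary outcomes closes with "as well as possible modifications in microbiota". The question therefore has main-objective status, although the Sample size section names the BMI Z score as the principal variable.

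Stool is "collected in a sterile container by parents at the beginning and at the end of the trial", so each child contributes a pair of samples. Under Microbiota analysis, "pyrosequencing of the PCR amplicons is performed using a Roche/454 GS Titanium technology platform", followed by taxonomic assignment. No target taxa are listed.

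The Statistical analysis section then says three things about these data: "the raw microbiologic data are reported as relative abundances"; "Differences among times, treatments and puberty are compared using the Mann-Whitney" U test; and "the clustering of the colonic microbiota in both of groups is calculated by a principal component analysis". The section's only multiplicity step, "A Bonferroni test will be used to assess the specific differences between the treatments", comes directly after the linear mixed model and before the genetic and microbiota paragraphs.

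**The concern.** The objective asks whether the community as a whole changes after treatment, and in a placebo-controlled trial that means whether it changes differently on metformin. The stated methods do not put that question.

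- **No test of the whole community.** PCA is an ordination without a null hypothesis. It cannot separate a difference between arms from chance.
- **No between-arm comparison of change.** Time and treatment are listed as separate factors. A before-after difference cannot be credited to metformin, because both arms also receive lifestyle advice. The mixed model for the other outcomes does contain a time-by-treatment term; the microbiota analysis names no counterpart.
- **No stated error control.** A Mann-Whitney test handles one abundance at a time, and untargeted sequencing yields many.

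At stake is the microbiota-mediated mechanism that the Background gives as a reason for the trial. A list of taxa found in this way could be largely chance and would be hard to interpret.

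**Working it through.** The article states no error rate, power or number of tests for the microbiota, so there is no figure of its own to reproduce.

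**Inputs.** The test and the treatment factor come from Statistical analysis. The number of taxa, m, is not given, so a range is assumed. The level per test is assumed to be 0.05 two-sided; the article states an α of 0.05 only for the BMI Z score. Only the treatment contrast is counted.

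**Independent taxa, no metformin effect.** The chance of at least one false difference is 1 − 0.95^m. The expected number of false taxa is 0.05 × m.

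| Taxa (m) | Chance of at least one | Expected number |
|---|---|---|
| 10 | 1 − 0.95^10 = 40% | 0.5 |
| 20 | 1 − 0.95^20 = 64% | 1.0 |
| 50 | 1 − 0.95^50 = 92% | 2.5 |
| 100 | 1 − 0.95^100 = 99% | 5.0 |

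To pass 95%, m must exceed ln(0.05)/ln(0.95) = 58.4, that is 59 independent taxa.

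**Correlated taxa.** A null simulation (1,500 runs) used 128 children, which is 160 less the planned 20% loss, split 64 against 64. End-of-trial values were compared by Mann-Whitney with equally correlated taxa. The chance of at least one p < 0.05 was:

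| Taxa | Correlation 0 | 0.3 | 0.6 |
|---|---|---|---|
| 20 | 65% | 56% | 36% |
| 50 | 93% | 81% | 54% |

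The lowest entry, 36%, is still about seven times the nominal 5%. Correlation does not alter the expected number of false taxa.

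**Effect of control across taxa.** With a Bonferroni level of 0.05/m, the chance becomes 1 − (1 − 0.05/20)^20 = 4.9% for 20 taxa and likewise 4.9% for 50. In the simulations, which also included 6 taxa, it stayed between 2.5% and 5.5%. Benjamini-Hochberg at 5% gives the same protection when no taxon differs and the tests are independent.

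**The time factor.** A Mann-Whitney test of before against after treats two samples from one child as if they came from two children. Simulated type I error was 1.8%, 0.9% and 0.1% at within-child correlations of 0.3, 0.5 and 0.7. That comparison loses power rather than producing extra false findings.

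**The case against.** The best reply is that this is a journal article with three sentences on the microbiota. Error control across taxa, the taxonomic level and a multivariate test are commonly left to the full protocol or analysis plan. That stands as far as it goes: the article does not say that taxa are tested without correction, only that no correction is stated. It does not excuse the methods the article does fix. Those are a single-abundance independent-samples test, applied factor by factor, and a PCA as the only whole-community method. A later plan would have to replace these, not just add detail.

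It can also be said that the PCA is never presented as a test. That is so, and describing clustering with it is not an error. The consequence is that the article states no inference at all on composition as a whole.

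A reader might infer more than the text supports:

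- **That a false microbiota finding is almost certain.** This depends on a taxon count the article does not give. For the treatment contrast it needs about 59 independent taxa to pass 95%, and more if taxa are correlated.
- **That the objective counts as met once any taxon is significant.** The article states no such criterion.
- **That the three factors can be pooled into one error rate.** Time and puberty differences may be real when metformin does nothing, and neither is evidence about metformin. The before-after test is also conservative.

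**Conclusion.** The point holds for the treatment contrast and for what the article states. A main objective about change in composition has no named test of the community and no named between-arm comparison of change. No error control across taxa is stated either.

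If taxa are each tested at 0.05, the chance of at least one false treatment difference runs from about 40% (10 independent taxa) to 99% (100). With between-taxon correlations up to 0.6 it can fall to 36% for 20 taxa and 54% for 50. These figures rest on the assumed level and taxon counts, on no metformin effect on any taxon, and on no correction being specified elsewhere. They describe a risk of uncertain size, not a near-certainty.

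The matter should be corrected. It does not affect the BMI Z score analysis.

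**What to change.** Reword the microbiota paragraph of the Statistical analysis section as follows.

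1. **Test for the fourth objective:** one global test of the between-arm difference in within-child community change from baseline to month 6. An example is PERMANOVA on a distance matrix of the children's changes, with treatment labels permuted within center, pubertal stage and sex. Center belongs in the scheme because allocation is half and half at each center, two of the four centers recruit only one pubertal stage, and the mixed model already adjusts for center. Table 1 gives 12 such cells of 10 or 20 children, which leaves room for permutation.
2. **Taxon level:** compare within-child change between arms at one pre-stated taxonomic level, with Benjamini-Hochberg control at 5% across all taxa tested.
3. **Description only:** keep the PCA as a display, and report time and puberty differences as descriptive.

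The cost is small. Both stool samples are already planned, the extra computation is minor, and the article reports recruitment still open, with the blind to be kept until the analyses are done. The price is that fewer individual taxa will reach significance.

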### Randomization

The participants are assigned to metformin or placebo in accordance with a randomization schedule generated by the Pharmacy Service of the Virgen de las Nieves University Hospital in Granada, with MAS 100 version 2.1 software (Glaxo-Welcome, Madrid, Spain) by the Support Consortium to Biomedical Research Network (CAIBER). At each center, 50 % of the children are assigned to each group.

The drug presentation format for the metformin and placebo groups has the same appearance. The local physician responsible for the procedure is only aware of the box/bottle codes of the tablets (as well as the registration number of the participating child). These codes have a corresponding equivalent available only to the coordinating investigator who has the other data of pharmaceutical interest, such as the origin, lot number and manufacturing and packaging dates (as well as whether the drug is metformin or placebo). The aforementioned local physician is not aware of these data and thus assigns the participant to one study group, without knowledge of the primary treatment administered.

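### Microbiota time points are paired within child but are compared with the independent-samples Mann-Whitney U test, and no between-arm test of change is stated

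*Protocol article*

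**What the plan says.** In the protocol article, the Objectives section lists four main objectives and states that "the fourth objective is to evaluate the change of gut microbiota composition after treatment". The Methods paragraph of the Abstract also names possible changes in microbiota among the primary outcomes.

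Under Blood, urine and fecal sampling, "100–200 g of fecal sample is collected in a sterile container by parents at the beginning and at the end of the trial". Every child therefore contributes two samples.

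The last paragraph of Statistical analysis gives the method for these data. It says that "the raw microbiologic data are reported as relative abundances", then: "Differences among times, treatments and puberty are compared using the Mann-Whitney" U test. It closes with a descriptive step: "the clustering of the colonic microbiota in both of groups is calculated by a principal component analysis". It names no paired test, no within-child change and no time × treatment term.

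Earlier in the same section, a linear mixed effects model with time × treatment among its fixed effects is given as the analysis of the treatment effect. The text does not say whether that model also covers the microbiota data.

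**The concern.** The Mann-Whitney U test suits two of the three comparisons it is assigned. Children on metformin and on placebo are different children, and so are pre-pubertal and pubertal children. Baseline and end-of-trial samples come from the same children. The test treats them as unrelated and so uses the wrong variance for the time comparison.

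The second issue is the contrast. Study design and Interventions give lifestyle and diet advice to all participants. A before-after shift within an arm therefore mixes any drug effect with the effect of advice, growth and time. Only a comparison between arms separates them, and the microbiota paragraph does not say that change, or a baseline-adjusted end value, is what will be compared.

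At stake is whether one of the four declared objectives is tested with the precision that the paired samples allow.

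**Working it through.** **Inputs.** From the documents: two samples per child; 40 children per puberty-by-treatment group, hence 2 × 40 = 80 per arm; 20 % expected loss, leaving 80 × 0.8 = 64 per arm or 40 × 0.8 = 32 per group. The α of 0.05 is stated for the BMI Z score and is used here two-sided. Assumed, because the documents give no figure for microbiota: the within-child correlation ρ, the 80 % reference power, and a shift of 0.4 SD in the simulation. The plan states no microbiota power figure, so there is none to reproduce.

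**Time comparison, normal approximation.** With equal variances σ² and n children, the mean before-after difference has variance 2σ²(1 − ρ)/n. An unpaired test uses 2σ²/n. Its statistic is the paired statistic multiplied by √(1 − ρ), so it rejects only when the paired statistic exceeds 1.96/√(1 − ρ). Hence:

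- true size = 2[1 − Φ(1.96/√(1 − ρ))]
- power = Φ(2.8016 − 1.96/√(1 − ρ)), where 2.8016 = 1.96 + 0.8416 is the shift at which a paired test has 80 % power.

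| ρ (assumed) | 1.96/√(1 − ρ) | true size | 2.8016 minus column 2 | power (paired: 80 %) |
|---|---|---|---|---|
| 0.3 | 2.343 | 1.9 % | 0.459 | 68 % |
| 0.5 | 2.772 | 0.6 % | 0.030 | 51 % |
| 0.7 | 3.578 | 0.03 % | −0.777 | 22 % |

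**Simulation of the rank tests themselves** (5,000 replicates, bivariate normal data, two-sided 0.05). With no true change and n = 64, Mann-Whitney rejects in 1.9 %, 0.8 % and 0.1 % of replicates at ρ = 0.3, 0.5 and 0.7. The signed-rank test stays near 5 %. The approximation is slightly too extreme at the higher correlations, but the direction is the same. Power for a 0.4 SD change:

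| ρ | n = 64: Mann-Whitney / signed-rank | n = 32: Mann-Whitney / signed-rank |
|---|---|---|
| 0.3 | 62 % / 74 % | 30 % / 44 % |
| 0.5 | 63 % / 87 % | 28 % / 58 % |
| 0.7 | 66 % / 98 % | 23 % / 79 % |

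**Arm comparison.** In units of 2σ²/n, the between-arm difference has variance 1 for end values, 2(1 − ρ) for change scores, and, in large samples, 1 − ρ² for baseline-adjusted end values.

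| ρ | end values | change | baseline-adjusted |
|---|---|---|---|
| 0.3 | 1 | 1.40 | 0.91 |
| 0.5 | 1 | 1.00 | 0.75 |
| 0.7 | 1 | 0.60 | 0.51 |

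Change beats end values only when ρ exceeds 0.5. Since 1 − ρ² = (1 − ρ)(1 + ρ), the adjusted variance never exceeds either of the others. The simulation agrees for the two unadjusted options: with 64 per arm and a 0.4 SD effect, Mann-Whitney on end values against change has power 60 % against 46 % (ρ = 0.3), 60 % against 59 % (0.5) and 59 % against 81 % (0.7).

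**The case against.** The defence against the second part is substantial. The microbiota sentence lists treatments as a comparison of its own and does not say whether end values or within-child changes are compared. If end values are meant, a Mann-Whitney test between randomized arms is a valid test of drug effect: randomization balances baseline in expectation, and advice given to both arms cancels. The mixed-model sentence is also not expressly limited to other outcomes. A reader might infer that the trial will never test microbiota change between arms. The document does not support that. It supports only that no such test is stated, although the separate microbiota paragraph suggests that the mixed model was not meant for these data.

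A reader might also infer that the authors would take significance in one arm and not in the other as a metformin effect. Nothing in the text says so. It does not even say whether the time tests are run within each arm.

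Finally, all sizes above are illustrative. Relative abundances can be skewed or contain many zeros, and the simulated data were normal.

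None of this rescues the time comparison. It is a stated choice of test, not a detail left to a fuller document, and the stated sampling scheme makes the data paired.

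**Conclusion.** The point holds in two parts of unequal strength.

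- **Time comparison:** wrong as written, with high confidence. An independent-samples test is assigned to paired samples. With positive within-child correlation the error is conservative. A reader might take the wrong error rate to mean false positives, but the figures show the opposite: size falls below 5 % and power is lost. For assumed ρ of 0.3 to 0.7, power is about 68 % to 22 % where a paired test would have 80 %. With 32 children, ρ = 0.5 and a 0.4 SD change, it is 28 % against 58 %.
- **Treatment comparison:** the plan does not state a between-arm test of change, although change is the objective. A comparison of end values would be valid but would discard the baseline samples.

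The size of the loss rests on the assumed correlation; its direction needs only that the correlation is positive. The sample size and the BMI Z score analysis are untouched. Because microbiota is one of four main objectives, the wording should be corrected.

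**What to change.** Reword the microbiota paragraph as follows:

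- **Time:** Wilcoxon signed-rank test on each child's two samples, within arm and labelled descriptive.
- **Treatment:** a between-arm comparison of end-of-trial abundance adjusted for baseline (suitably transformed or rank-based), or a mixed model with time × treatment. Unadjusted change scores are not an equal substitute, since they have less power than end values when ρ is below 0.5.
- **Mann-Whitney U:** only for comparisons between different children.

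Log-ratio scaling and false-discovery-rate control across taxa may be considered as extras; they are not part of this error.

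The cost is analysis wording, with the same samples and measurements. Trial status says that recruitment continues, and Breaking of the study blind keeps the allocation concealed until the analyses are complete, so the change can be made and dated before unblinding.

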### Interim analyses and stopping rules

Interim or preliminary analyses during the course of this RCT are not planned. In the event of subject withdrawal, a replacement or substitution is not planned; thus, these participants will be considered lost. The data associated with these subjects will subsequently be excluded from the statistical analysis. For this reason, the calculation of the sample size has included a potential loss of up to 20 %.

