**Fig. 1 Fig1:**
[figure not shown]
Participant flow diagram. *PPG* pre-pubertal girls; *PPB* pre-pubertal boys; *PG* pubertal girls; *PB* pubertal boys

**Table 1 Tab1:** Distribution of patients according to center

Hospital	Total (160)
Reina Sofía (Córdoba)	20 pre-pubertal girls
	20 pre-pubertal boys
Virgen de las Nieves (Granada)	10 pre-pubertal girls
	10 pre-pubertal boys
	10 pubertal girls
	10 pubertal boys
Clínico Universitario (Santiago de Compostela)	10 pre-pubertal girls
	10 pre-pubertal boys
	10 pubertal girls
	10 pubertal boys
Lozano Blesa (Zaragoza)	20 pubertal girls
	20 pubertal boys

Children are randomly assigned to receive metformin or placebo for six months. Both treatments are administered during meals (to minimize gastrointestinal side effects and the risk of hypoglycemia). The participants’ parents are given a coded vial of pills that contains either metformin or placebo pills for two months. The concealed allocation process ensures that the participants and all investigators are unaware of the allocated treatment. All participants are offered lifestyle intervention advice at all visits.

The clinical hospitals that participate in the RCT form part of the Maternal and Child Health and Development (SAMID network). Moreover, the RCT has been registered in the European Clinical Trials Database on 14 November 2011 (EudraCT, ID: 2010-023061-21).

In accordance with the “International Conference on Harmonization of Technical Requirements for Registration of Pharmaceuticals for Human Use” Guide (ICH): “CPMP/ICH/291/96 Note for Guidance on General Considerations for Clinical Trials,” this is a phase III clinical trial because it involves a commercialized drug for which a new indication that is not included in its technical specifications will be investigated.

The CONSORT statement (Consolidated Standards of Reporting Trials) has been taken into account in the study design report, as well as for the abstract and the flow diagram (Fig. 1), thereby increasing the reporting quality for the RCT. Moreover, the Standard Protocol Items: Recommendations for Interventional Trials (SPIRIT) guidelines for this study protocol are attached in Additional file 1.

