### Interventions

The patients are instructed to taking a initial dose of 50 mg twice daily for 10 days, followed by 500 mg twice daily until the end of the treatment. The presentation comprises tablets in opaque, white plastic containers and a side label with 28 units. The dietician centers administer a food frequency questionnaire (FFQ) and a physical activity survey to all participants at the beginning and at the end of the trial. All participants are provided with standardized healthy lifestyle advice at the start of a one-on-one session, including a healthy diet and exercise advice sheet. The participants attend an initial trial baseline visit, followed by three additional visits at 2-month intervals (Fig. 2), which include anthropometric parameter and blood pressure (BP) assessments, as well as a physical examination. A medical history is obtained for each participant, including documentation of the family history.

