### Adverse effects and co-medication

To assess the safety of metformin administration, the primary evaluation criteria are the absence of the adverse effects (AEs) described. The patients are assessed regarding all symptoms at each visit to identify potential AEs and the use of co-medication in the previous two months. A contact number is provided to enable enquiries regarding any symptom perceived as adverse. At this number, the patient is informed about what to do in the event of an adverse reaction. They are also requested to suspend the medication. The following information is recorded: description, date of onset and end date, severity, assessment of relation to the study medication, other suspect drug or device and action taken. Follow-up information should be provided as necessary. The prominent AEs are as follow: diarrhea, nausea, blood in the stools, headache, dizziness, general discomfort, sleepiness, cold or flu, pharyngitis, otitis, allergic episode, lactic acidosis, urea increment, hypercreatininemia, hypertransaminasemia and vitamin B_12_ deficiency, as well as any other symptoms reported by the participants. The relationships of the AEs to the study medication will be assessed by a qualified medical investigator.

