### Sample size

As previously indicated, the principal variable is the BMI *Z* score, on which the sample size calculation was based. Its standard deviation is 2.29 in the least favorable case (according to the tables by Cole et al. [29]), and a desired minimum difference of 2 points is expected. With an *α* error of 0.05, a β error of 0.20 and an estimated follow-up loss of 20 %, four groups in total are planned for the study: two groups of obese children (pre-pubertal and pubertal) treated with metformin and two groups of obese children (pre-pubertal and pubertal) treated with a placebo; there is a requirement of at least 40 patients per group (× four groups = 160 children total).

The clinical argument for the choice of the principal variable adheres to the fact that the obesity concept is based on the BMI, as the bibliography endorses. However, it should be noted that the BMI in childhood changes substantially with age [30]. Thus, age- and sex-specific cut-off points are needed to define pathology in children via means of a *Z* score [29] to obtain a more accurate value.

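### Excluding all data from children who withdraw makes the BMI Z score comparison completers-only, with possible bias in either direction

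*Protocol article*

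**What the plan says.** The rule is in the protocol article under Interim analyses and stopping rules: "In the event of subject withdrawal, a replacement or substitution is not planned; thus, these participants will be considered lost". The next sentence reads: "The data associated with these subjects will subsequently be excluded from the statistical analysis". The article then offers the sample size as cover: "the calculation of the sample size has included a potential loss of up to 20" per cent.

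Four other places bear on it:

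- **Interventions:** a baseline visit is "followed by three additional visits at 2-month intervals", with anthropometry at these visits. A child who leaves after month 2 or 4 therefore already has post-baseline BMI Z scores.
- **Statistical analysis:** the treatment effect is estimated with a linear mixed effects model that has time and time × treatment among its fixed effects.
- **Study design:** tablets are taken with meals "to minimize gastrointestinal side effects and the risk of hypoglycemia".
- **Adverse effects and co-medication:** diarrhea and nausea are among the listed effects. Of patients who call about a reaction, the article says: "They are also requested to suspend the medication".

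The article describes no analysis set of all randomised children, no use of partial records and no sensitivity analysis that would soften the exclusion.

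**The concern.** Randomisation makes the arms comparable at baseline. Removing children because of a later event keeps that comparability only if leaving is unrelated to outcome, or if it selects children in the same way in both arms. The article itself gives reasons to doubt this: the drug has expected gastrointestinal effects, and reported reactions lead to a request to stop the tablets. Children who leave the metformin arm may differ from those who leave the placebo arm in how their BMI was developing.

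The rule also gives up the main advantage of the chosen model. A likelihood-based mixed model accepts incomplete records and is valid when dropout depends on values already observed. Deleting those records replaces that condition with a stronger one.

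At stake is the principal efficacy result. No analysis described in the article would show a reader whether the exclusion had moved it.

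**Working it through.** **1. The planned loss.** The inputs are 160 children, 40 in each of four groups, and 20 % loss (Sample size).
- Removed: 0.20 × 160 = 32. Analysed: 128, or 0.80 × 40 = 32 per group.

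**2. Is the harm lost power?** The inputs are a difference of 2, SD 2.29, α 0.05 (taken as two-sided) and "a β error of 0.20".
- n per group = 2 × (1.960 + 0.842)² × 2.29² / 2² = 20.6, so 21. With loss, 21 / 0.80 = 26.25, so 27. The stated 40 is not reproduced but is larger. That is a separate matter.
- Power = Φ(2 / (2.29 × √(2/n)) − 1.960).
- n = 40: 2 / 0.512 = 3.906, giving Φ(1.946) = 97.4 %.
- n = 32: 2 / 0.5725 = 3.493, giving Φ(1.533) = 93.7 %.

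On the plan's own inputs, power after the exclusion stays above 80 %. The issue is bias.

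**3. How large could the bias be?** The documents give no withdrawal rates by arm and no link between withdrawal and response, so everything in this step is assumed. Let X be the standardised 2-month change in BMI Z (higher is worse) and Y the 6-month change with SD 1. Their correlation is 0.6 and there is no true treatment effect. Let P(leave | X) = expit(a + bX), with a set in each arm to give the withdrawal rate. Then:

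completers' mean = 0.6 × E[X × (1 − P(leave | X))] / (1 − rate)

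By numerical integration (negative differences favour metformin):

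| Withdrawal, metformin / placebo | Link to response (b) | Completers' means | Difference (truth 0) |
|---|---|---|---|
| 30 % / 10 % | 1.2 in both arms | −0.172, −0.063 | −0.11 |
| 25 % / 15 % | 1.2 in both arms | −0.145, −0.091 | −0.05 |
| 20 % / 20 % | 1.2 in both arms | −0.118, −0.118 | 0.00 |
| 20 % / 20 % | 1.2 metformin, 0 placebo | −0.118, 0 | −0.12 |
| 30 % / 10 % | −1.2 in both arms (better responders leave) | +0.172, +0.063 | +0.11 |
| 30 % / 10 % | 0.4 in both arms | −0.070, −0.024 | −0.05 |
| 30 % / 10 % | 0 | 0, 0 | 0.00 |

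For a true benefit of 0.50 SD, the first row gives 0.50 + 0.11 = 0.61, which is 0.11 / 0.50 = 22 % too large. The fifth row gives 0.50 − 0.11 = 0.39.

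A separate simulation, with correlation 0.8 between adjacent visits, log-odds 1 per SD in metformin and random withdrawal on placebo, gave −0.11 SD at 20 % / 20 %, −0.13 at 25 % / 15 % and −0.16 at 30 % / 10 %.

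**4. What do the discarded visits recover?** When the 2-month values of children who left were used in these simulations, the estimate was within 0.01 SD of the truth. That follows from the set-up, because dropout was generated from the observed 2-month value. It shows what the model can do under missing at random, not that the assumption holds here.

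**The case against.** The best case against the point concerns its reach, and much of it stands.

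- **Suspending tablets is not stated to be withdrawal.** A reader might infer that any child who stops for a reaction is excluded. The article does not say so, and it leaves withdrawal undefined. Adherence enters the model as a fixed effect, and tolerance is reported against the dose level reached (Adherence and tolerance). Both suggest that children taking less drug stay in. The route from intolerance to exclusion is plausible, not stated. Even if withdrawal means only leaving the study, the analysis is still completers-only.
- **Overstated efficacy is not established.** A reader might infer that the exclusion flatters metformin. The sign depends on who leaves, which the documents do not say. With no link to response there is no bias.
- **Loss of adverse-event data is only one literal reading.** The exclusion names the statistical analysis, while adverse events have their own recording and summary provisions. The text is ambiguous on this, and the main point does not depend on it.
- **Balanced withdrawal is not a safeguard.** A reader might take equal rates as reassurance. The 20 % / 20 % rows show that this holds only if the reasons for leaving act alike in both arms.
- **The remedy has limits.** A child who leaves before month 2 has no scheduled post-baseline BMI Z score. Intolerance need not act through observed BMI Z. Blood, urine and fecal samples are taken only at the start and end.

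One defence fails: that an unseen analysis plan may deal with this. The sentence is a positive instruction, and a plan that kept the data would contradict it.

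**Conclusion.** The point holds for the principal variable. As written, the rule turns the BMI Z score analysis into a completers-only comparison. Up to 32 of 160 children are removed after randomisation, and observed 2- and 4-month values are discarded although the stated model can use them. The 20 % allowance restores numbers, not the randomised comparison.

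The bias can go either way, and its size cannot be derived from the documents. The figure of about 0.11 SD is an illustration. It rests on a change SD of 1, correlation 0.6, log-odds of 1.2 per SD and 30 % against 10 % withdrawal; other assumptions in the table give anything from none to 0.12 SD. It should not be converted to BMI Z points using the article's SD of 2.29, which is not given as the SD of the six-month change.

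The documents do not support the stronger conclusions that metformin's effect will be overstated or that safety data will be lost. The sentence still needs to be changed, because it governs the main result and nothing else in the article offsets it.

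**What to change.** Replace the exclusion sentence under Interim analyses and stopping rules with:

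> All randomised children are analysed in the assigned arm; all BMI Z scores observed up to withdrawal enter the linear mixed model under missing at random.

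Then:

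1. Make completers-only a sensitivity analysis.
2. Add a simple sensitivity analysis for data missing not at random, for example one that shifts the unobserved values of children who left by a stated range, separately by arm.
3. State that the exclusion does not apply to adverse-event summaries, which cover every child who took study medication.
4. Say that the 20 % allowance concerns precision only.

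The gain is for BMI Z score and other measures taken at interim visits. Biomarkers and microbiota, sampled only at the start and end, benefit little.

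The cost is analysis wording, with no extra children or visits. The article reports that recruitment is continuing, so the change can be made before the blind is broken.
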